**Screening/Day 0 and Day 1 procedures can occur on the same day.**

The SARS-CoV-2 positive test results will be confirmed through laboratory records.

**10.1.7. Day 2 Through Day 13**

The participant will do the following every day from Day 1 through Day 13, inclusive:

- Collect mid-nasal swab for PCR on Day 3, Day 5, Day 7 and Day 10. (Swab collection may be decreased to Day 5 and Day 10 in participants where multiple swabbing is not feasible.)
- Take study therapy (as assigned)
- Complete Daily Survey (online, telephone, or text messaging). This Survey will include confirmation of adherence to study therapy dosing and daily swab collection, concomitant medication review, AEs, and symptoms review and objective measures including SpO2, respiratory rate, temperature and pulse. In addition, the Transitional Dyspnea Survey will be completed.
- *If in DBS Sub-study, collect DBS samples for analysis of concentration of assigned experimental intervention at any time during this period (1 to 5 times) after study drug dosing has commenced. No more than 1 sample per day should be collected.*

A study team member will be available via Telehealth, text messaging, or telephone to provide support for completion of study procedures. The driver will collect the swabs as required.

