| Adverse Events (AEs)                                                                         |                                                  | X                                     | X                             | X                            | X                             | X                            | X                             | X                             | X                             |                               |                                                        |
| Dyspnea Scale (WURSS-11)                                                                     |                                                  | X                                     | X                             | X              | X               | X              | X               | X               |                               |                               |                                                        |
| Tisdale scale                                                                                |                                                  | X                                                   |                               |                              |                               |                              |                               |                               |                               |                               |                                                        |
| EQ-5D-5L                                                                                     |                                                  | X                                     |                               |                              |                               |                              |                               |                               | X               |                               | X                                        |

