|----------------------------------------------------------------------------------------------------------------------------------------------------------------------------------------------------------------------------------------|------------------------------------------------------------------------------------------------------------------------------------------------------------------------------------------------------------------------------------------------------------------------------------------------------------------------------------------------------------------------------------------------------------------------------------------------------------------------------------------------------------------------------------------------------------------------------------------------------------------------------------------------------------------------------------------------------------------------------------------------------------|
| 
 
To test whether any of the experimental interventions decrease resolution rate for symptomatic SARS-CoV-2 infection / COVID-19 disease
 
                                               | 
 
Proportion of days with fever after randomization
 
Proportion of days with respiratory symptoms after randomization
 
Time until clinical improvement (up to 28 days), defined normalization of temperature, respiratory rate, SaO2, and cough relief (> 50 in relation to baseline measured on a visual analog scale) in the last 72 hours;
 
Reduction in the perception of dyspnea (upper respiratory tract respiratory symptoms scale - WURSS-11) on days 0, 3, 7, 14 and 28 days;
 
Time to clinical failure, defined as time to need for hospitalization due to dyspnea, death, need for mechanical ventilation, shock with need for vasoactive amines;
 
 |

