## **10. Study Encounters**

### **10.1. For Brazil**

The current COVID-19 pandemic has placed a significant burden on the healthcare system. For this study, specimen and data collection will be conducted to minimize impact of non-ill participants within the healthcare system. If the participant is assessed as eligible, contact between study participants and study personnel will occur in person should the participants are identified at primary care setting, via a telephone, or through home visits by local physician assistants and medical students with PPE.

Participants will be instructed to seek clinical care should they manifest any signs or symptoms of LRTI requiring medical intervention.

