#### **10.1.2. Day 1 Through Day 14**

The participant will do the following every day from Day 2 through Day 14 (unless stated otherwise), inclusive:

- Take study therapy (for a total treatment of 10 days of treatment)
- Tolerance towards the assigned therapy
- Confirmation of adherence to study therapy dosing (Day 10)
- Daily dosing time from the day prior
- Reporting of adverse events
- Cardiac measurement using Kardiamobile monitors (Day 3, Day 7, Day 10, and Day 14)
- Pulseoximeter measurements (Day 3, Day 7, Day 10, and Day 14)

| Harmonized protocol document                                                          |
|---------------------------------------------------------------------------------------|
| Short title: Outpatient Management of SARS-CoV-2 for High-Risk Adults in LMICs |

- Measurement of heart rate (pulse oximeter) at rest after the participant remained seated at rest for 5 minutes
- Review of clinical symptoms and hospitalization
- WURSS-11 survey for dyspnea

A study team member will be available via Telehealth, text messaging, or telephone to provide support for completion of study procedures. Participants will be clinically assessed for signs and symptoms of respiratory distress and will have in person assessment of AEs. As needed, additional contact with the study clinician or staff will be conducted at the request of the participant (e.g., if developing concerning symptoms or an adverse event) or if needed to clarify study procedures or follow-up symptoms.

The health care provider will make home-visits to collect nasal-swabs or saliva samples for RT-PCR on Day 3, Day 7, Day 10, and Day 14. These samples collected on Day 14 will be used to analyse the viral shedding related outcomes. Other samples collected on Day 3, Day 7 and Day 10 will be stored for a biobanking deposit.

A study team member will be available via Telehealth, text messaging, or telephone to provide support for completion of study procedures.

Clinical outcomes will be confirmed through the electronic health record, if possible.

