**The participant will do the following on Day 1:**

- Take study therapy (as assigned)
- Complete Daily Survey (online, telephone, or text messaging). This Survey will include confirmation of adherence to study therapy dosing and daily swab collection, concomitant medication review, and symptoms review and objective measures including SpO2, respiratory rate, temperature and pulse. In addition, the Baseline Dyspnea Index survey will be completed.

*Instructions for skin puncture and DBS sample preparation are provided in Appendix 4. A study team member will be available via Telehealth, telephone, or text messaging to provide support for completion of this study procedure.*

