## **11. Study Assessments and Procedures**

- Study procedures and their timing are summarized in the SoA.
- Protocol waivers or exemptions are not allowed.
- Immediate safety concerns should be discussed with the sponsor immediately upon occurrence or awareness to determine if the participant should continue or discontinue study treatment.
- Adherence to the study design requirements, including those specified in the SoA, is essential and required for study conduct.
- All baseline evaluations must be completed and reviewed to confirm that potential participants meet all eligibility criteria. The Investigator will maintain a screening log to record details of all participants screened and to confirm eligibility or record reasons for screening failure, as applicable.
- Procedures conducted as part of the participant's routine clinical management and obtained before signing of the informed consent form may be utilized for screening or baseline purposes provided the procedures met the protocol-specified criteria and were performed within the time frame defined in the SoA.
- *Blood samples will only be collected as a part of a sub-study. The maximum amount of blood collected from each participant over the duration of the study, including any extra assessments that may be required, will not exceed 10 mL.*

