**11.1.3. Patient reported outcomes**

Results questionnaires reported by patients (EQ-5D-5L and Dyspnea scale - WURSS-11) will be answered by the participants before the study team carries out any study or clinic evaluation to avoid influencing the participants' responses. Study coordinators will review the participant's responses immediately after the participant completes the questionnaires to ensure that all questions are answered.

**Questionnaire EQ-5D-5L:** The EQ-5D-5L questionnaire consists of 5 questions, each with five levels (eg, no problems, mild problems, moderate problems, serious problems and extreme problems) representing 5 health domains: mobility, self-care, activities symptoms, pain and / or discomfort, and anxiety and / or depression. The EQ-5D-5L questionnaire also includes a visual analog scale that records the self-assessment of the participant's health status, graded on a scale ranging from 0 to 100, with higher scores indicating greater health-related quality of life. Participants must complete the EQ-5D 5L questionnaire as indicated in the event schedule.

**WURSS-11 scale** (Wisconsin Upper Respiratory Symptom Survey -11):

<https://www.fammed.wisc.edu/files/webfm-uploads/documents/research/wurss-11.pdf>

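### The secondary dyspnea endpoint is defined on WURSS-11, but a second Brazil visit schedule, copied in Section 8.1, requires two other dyspnea questionnaires that no endpoint uses, and no schedule collects the day 28 value

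*Protocol*

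**What the plan says.** Section 4.1 lists as a secondary endpoint: "Reduction in the perception of dyspnea (upper respiratory tract respiratory symptoms scale - WURSS-11) on days 0, 3, 7, 14 and 28 days". The Synopsis carries the same line. The Schedule of Activities (2.1) has one dyspnea row, for WURSS-11, marked from baseline through Day 14 and blank from Day 28 on. Section 10.1.1 asks for WURSS-11 on Day 0, and 10.1.2 lists "WURSS-11 survey for dyspnea" among the tasks for the days up to Day 14. On patient-reported outcomes, 11.1.3 names two instruments only: "Results questionnaires reported by patients (EQ-5D-5L and Dyspnea scale - WURSS-11) will be answered by the participants".

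Under the same heading, "10.1. For Brazil", a second set of visits begins at 10.1.6. For Day 1 it says "In addition, the Baseline Dyspnea Index survey will be completed". Section 10.1.7, headed Day 2 through Day 13, says "In addition, the Transitional Dyspnea Survey will be completed". WURSS-11 appears nowhere in 10.1.6 to 10.1.11. The same text is reproduced as 8.1.1 to 8.1.6, inside the section on discontinuation of study treatment. No sentence says which of the two Brazil schedules applies.

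**The concern.** The protocol gives sites two sets of day-by-day instructions that disagree on how dyspnea is measured, and only one set uses the instrument on which the endpoint is defined. The Baseline Dyspnea Index and the Transitional Dyspnea Survey appear in neither endpoint table nor in the protocol's statistical section, and nothing says how their scores relate to WURSS-11.

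Two things are at stake. Where both schedules are followed, sick outpatients fill in extra questionnaires with no stated use. Where only the second is followed, the dyspnea endpoint has no data, and a patient-reported score not taken on its day cannot be recovered afterwards.

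**Working it through.** No arithmetic applies, because the point depends on no rate, power or sample size. The check sets the five endpoint days in Section 4.1 against each place that schedules a dyspnea measurement.

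| Endpoint day | Schedule of Activities | 10.1.1 to 10.1.5 | 10.1.6 to 10.1.11 (copied in 8.1.1 to 8.1.6) |
|---|---|---|---|
| 0 | WURSS-11 | WURSS-11 (10.1.1) | none in the Day 0 list; Baseline Dyspnea Index on Day 1 |
| 3 | WURSS-11 | WURSS-11 (10.1.2) | Transitional Dyspnea Survey (10.1.7) |
| 7 | WURSS-11 | WURSS-11 (10.1.2) | Transitional Dyspnea Survey (10.1.7) |
| 14 | WURSS-11 | WURSS-11 (10.1.2) | none named (10.1.9) |
| 28 | blank | none named (10.1.3) | none named (10.1.10) |

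Three results follow.

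1. WURSS-11 is available on 4 of 5 endpoint days from the Schedule of Activities, on 4 of 5 from the first visit schedule, and on 0 of 5 from the second.
2. The second schedule's own instruments could not stand in for the endpoint even if someone tried to substitute them. They are absent on days 0, 14 and 28. If Day 0 and Day 1 are combined, as that schedule allows, they are still absent on days 14 and 28.
3. Day 28 is missing everywhere. The Day 28 visit in 10.1.3 lists EQ-5D-5L and a review of adverse events, symptoms and hospitalization, but not WURSS-11. This gap affects every patient, including those at a site that follows the Schedule of Activities exactly.

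Other lines show that the second schedule as a whole was not reconciled with the Brazil plan:

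- It adds a Day 5 swab and lets the Day 14 swab be omitted. Section 10.1.2 has swabs on Days 3, 7, 10 and 14 and uses the Day 14 sample for the viral shedding outcomes.
- It reimburses participants on Day 14, while Section 13.1 says there is no reimbursement in Brazil.
- It relies on a monitoring kit given to the participant and a study driver, while 10.1.1 and 10.1.2 describe measurement and sampling at home visits.

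The text is current and is not an accident of layout. The table of contents lists both sets of visits under the Brazil encounters. It lists no visit schedule in Section 8, which suggests that the copy there is misplaced.

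**The case against.** The strongest answer is that the controlling text agrees with itself. Both endpoint tables, the Schedule of Activities, 10.1.1, 10.1.2 and 11.1.3 all name WURSS-11. Section 11 says "Study procedures and their timing are summarized in the SoA", and Sections 9 and 11 both make adherence to that schedule mandatory. A site that collected no WURSS-11 would be in breach of it, and a site that followed everything would still have the endpoint through Day 14.

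This stands as a limit on the consequence. A reader might infer that the endpoint is lost at some sites, or attach a share of lost patients and turn it into a loss of precision. The documents do not support that: nothing indicates that any site works from the second schedule alone, and no figure for such a share is given. Participants are also randomized individually (Section 7.4), so values missing for a whole site would fall on all of its arms and would mainly cost precision rather than bias the comparison.

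A reader might also argue that the instruments cannot be pooled because of how a baseline and transition pair is scored. The protocol does not describe either questionnaire, so that argument has no footing here. What can be said is that they are differently named, no endpoint uses them, and no conversion is given.

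The objection does not remove the contradiction. The Schedule of Activities is described as a summary, whereas 10.1.6 and 10.1.7 are direct instructions to participants under the Brazil heading. It also leaves the day 28 gap untouched, because the Schedule of Activities is itself one of the places where day 28 is missing.

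**Conclusion.** The contradiction holds. One part of the operative text requires WURSS-11 for dyspnea, and another part, present twice, requires two different questionnaires and omits WURSS-11. The certain effect is that a site following the whole protocol collects questionnaires with no stated use. The possible effect is missing WURSS-11 values at a site that works from the second schedule alone; its extent cannot be estimated from the documents. The day 28 omission is separate and applies to all patients as the schedules stand.

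The endpoint is one of several secondary endpoints. The stated power calculations concern hospitalization and LRTI, so the primary endpoint and the sample size are unaffected. The dyspnea lines are best seen as one symptom of an unreconciled duplicate schedule. The conclusion rests on the protocol text alone; the statistical analysis plan was not available, but an analysis plan could not supply scores that were never collected.

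**What to change.** Remove the duplicate schedule in 8.1.1 to 8.1.6 and 10.1.6 to 10.1.11, or reconcile it with 10.1.1 to 10.1.5 and the Schedule of Activities. Exchanging the dyspnea lines alone would leave the other conflicts in place. Use one dyspnea instrument throughout: WURSS-11, as the endpoint and the Schedule of Activities state, unless the sponsor changes the endpoint itself, in which case Section 4.1, the Synopsis, the Schedule of Activities and 11.1.3 must change with it.

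Then align the time points. Either add WURSS-11 at Day 28 to the Schedule of Activities and to 10.1.3, or drop day 28 from the endpoint in Section 4.1 and the Synopsis.

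The cost is wording. No patients or visits are added. Removing the two unused questionnaires reduces burden, and adding WURSS-11 at Day 28 would put one short questionnaire into a contact already planned. The change should be made before sites build their forms or, if enrolment has begun, by prompt clarification.

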**10.1.8. Days 3, 8 and 14 (+/-1 day)**

Contact with study clinician or staff will be conducted via telemedicine (Telehealth) or telephone. Participants will be clinically assessed for signs and symptoms of respiratory distress and will have in person assessment of AEs. As needed, additional contact with the study clinician or staff will be conducted at the request of the participant (e.g., if developing concerning symptoms or an adverse event) or if needed to clarify study procedures or follow-up symptoms.

|                                          |                 |
|------------------------------------------|-----------------|
| Date/version: May 19, 2020 – V1.0 | Page: 40 |
|------------------------------------------|-----------------|

#### **10.1.9. Day 14**

The participant will do the following on Day 14:

- Collect mid-nasal swab for PCR (May be omitted in participants where multiple swabbing is not feasible).
- Complete Daily Survey (online, telephone, or text messaging). This Survey will include confirmation of adherence to study therapy dosing and daily swab collection, concomitant medication review, and symptoms review and objective measures including SpO2, temperature and pulse.
- 
- *If in DBS Sub-study, collect DBS samples for analysis of concentration of assigned experimental intervention, if not already collected.*

A study team member will be available via Telehealth, text messaging, or telephone to provide support for completion of study procedures.

Clinical outcomes will be confirmed through the electronic health record, if possible.

#### **10.1.10. Day 28, 56 and 90**

Participants will be contacted on days 28, 56 and 90 to determine well-being. On day 56 a DBS may be collected to determine antibody development

#### **10.1.11. Participant Reimbursement**

Participants will be reimbursed on Day 14. No reimbursement will be provided to index cases for questionnaire completion and referral of their close contacts. No reimbursement will be provided for unscheduled Telehealth visits requested by the participants for support with study procedures.

## **11. Study Assessments and Procedures**

- Study procedures and their timing are summarized in the SoA.
- Protocol waivers or exemptions are not allowed.
- Immediate safety concerns should be discussed with the sponsor immediately upon occurrence or awareness to determine if the participant should continue or discontinue study treatment.
- Adherence to the study design requirements, including those specified in the SoA, is essential and required for study conduct.
- All baseline evaluations must be completed and reviewed to confirm that potential participants meet all eligibility criteria. The Investigator will maintain a screening log to record details of all participants screened and to confirm eligibility or record reasons for screening failure, as applicable.
- Procedures conducted as part of the participant's routine clinical management and obtained before signing of the informed consent form may be utilized for screening or baseline purposes provided the procedures met the protocol-specified criteria and were performed within the time frame defined in the SoA.
- *Blood samples will only be collected as a part of a sub-study. The maximum amount of blood collected from each participant over the duration of the study, including any extra assessments that may be required, will not exceed 10 mL.*

### **11.1. Efficacy Assessments for Brazil**

#### **11.1.1. Mid-nasal swab or saliva for Brazil**

Health care providers will collect mid-nasal swabs or saliva samples from participants for viral detection at Day 1, Day 3, Day 7, Day 10 and Day 14 (+/-1 day).

Swabs or saliva will be subjected to RNA amplification and tested for SARS-CoV-2 by the local laboratory or by a laboratory designated by it.

#### **11.1.2. Participant Survey for Brazil**

Participants will be asked to complete Surveys (Daily Survey) that will include questions about symptoms from both the drug regimen, review of concomitant medications.

##### **11.1.2.1. Vital signs assessment**

The participant should avoid eating, smoking or exercising for 30 minutes before collecting vital signs measurements. The participant must remain seated and at rest for approximately 5 minutes before the measurement.

##### **11.1.2.2. Heart rate**

Heart rate must be measured for a total of 60 seconds, or as stipulated, with pulse oximeter device or Kardiamobile device.

**11.1.2.3. Physical examination:**

The basic physical exam will be performed at baseline. The following body systems will be examined:

- Cardiovascular examination
- Lungs and chest, including breathing
- Head and neck
- the abdomen
- Musculoskeletal disorders
- Skin
- Neurological assessment

Any new clinically significant physical examination abnormalities identified during the study should be reported as an AE.

